### Recruitment and randomisation procedures

Teams will be recruited into the trial over a 12 month period, at a rate of 5-6 SLaM teams every three months and 4-5^2^gether teams every five months. One of the aims of this trial is to establish whether this planned recruitment rate is feasible. The service user baseline assessment measures are anticipated to take up to 90 minutes, so if necessary will be completed in two face to face meetings with researchers. The generic staff baseline assessment will take up to 20 minutes and the paired staff baseline assessment measures will take an additional 20 minutes per service user. They will either be completed at the community base or within the service user's own home, at a mutually agreed time.

Participating teams will be randomly allocated on an equal basis to intervention (N = 15) and control groups (N = 14). Allocation will be stratified by site (six sites: four SLaM Boroughs, two^2^gether localities) to ensure balance. Randomisation will be undertaken using processes set out by the independent Mental Health and Neuroscience Clinical Trials Unit, on the basis of a team identification number and site information. Service users will be allocated based on these clusters.

The clinical information system will be accessed by either Clinical Studies Officers (CSOs) from National Institute for Health Research (NIHR) Mental Health Research Network (MHRN), information analysts or the researchers acting under arrangements with the responsible Trust to compile the list of names, diagnoses, ethnicity and date of births for randomisation. This will be the only access to clinical information by the research team prior to consent.

In^2^gether, a randomly ordered list of service users on the caseload of each team with a clinical diagnosis of psychosis will be generated using the same procedures as set out by the Clinical Trials Unit. The first 15 service users will be selected from the randomly ordered caseload list. In SLaM, two randomly ordered lists of service users with a psychosis diagnosis on the caseload of the team will be generated using a random number table. One list (List A) will comprise service users who come from service users who are from black African, black Caribbean and black other backgrounds, and the other list (List B) will comprise all other service users. The first 6 service users from list A and the first 9 from list B will be selected, giving a total sample of 15 per SLaM team. This will ensure epidemiological representativeness in the sample in relation to black ethnicity, and will ensure sufficient power to test the secondary study hypothesis.

If an individual does not meet inclusion criteria or refuses consent to participate, then the next person from the appropriate randomly-ordered list will be chosen. Caseload randomisation will be undertaken using procedures set out by the Mental Health and Neuroscience Clinical Trials Unit, on the basis of a service user identification number.

### Approaches to minimise bias

Due to the nature of the intervention, neither clinicians nor service users can be blinded to allocation status. However, several approaches have been used to minimise bias.

Addressing bias at allocation

1. All randomisation will be undertaken by the research team following procedures set out by the independent Clinical Trials Unit which has been awarded full CTU registration by UKCRC. Identifying information about teams or service users will not be known before randomisation.

Addressing bias in baseline data

2. Baseline data from staff and service users will as far as feasible be collected before allocation, to avoid bias based on allocation status

Addressing bias in the intervention

3. The research team will monitor implementation across sites, in order to maximise fidelity and ensure comparability of the intervention between sites.

4. Change in staff for each team will be carefully monitored, with particular attention paid to identifying staff that move between teams in different allocation arms. This will allow contamination to be estimated.

Addressing bias in follow-up data

5. All included services users will be followed up and included in the analysis using intention-to-treat approaches, reducing the impact of selective attrition.

6. At follow-up assessment, participants will be asked not to reveal their allocation status, and at the end of the interview the rater will record their guess about the service user's allocation status. This will allow researcher blindness to be estimated.

7. Follow-up data will where possible be collected by CSOs from the National Institute for Health Research Mental Health Research Network (MHRN). This will increase the likelihood of rater blindness.

8. Bias in the outcome data will be minimised by the use of standardised objective assessments, and informed by previous outcomes research [30,31].

9. Some evaluation data will be obtained from casenotes, thus reducing the possibility of respondent bias. More generally, the multi-method approach to evaluation includes data collected from staff, service users, researcher ratings, and case note audit. This reduces the impact of bias in any individual data source.

10. The focus group process evaluation data, for which unblinding will be necessary as only intervention group participants are involved, will be collected after the follow-up outcome evaluation data.

11. Protected data storage with clear access protocols in line with Good Clinical Practice Guidelines [32] will be used to store allocation and outcome data separately.

Addressing bias in analysis

12. No data regarding the allocation status will be stored in the data entry database

13. All data will be stored in either a locked filing cabinet or in an electronic password-protected database.

14. The primary data analysis will be undertaken blind to allocation status

15. Allocation status will coded as A and B in all data requests.

### Control

All participating teams provide care co-ordination for clients. The framework for care co-ordination and resource allocation in mental health care is the Care Programme Approach (CPA) [33]. The CPA process is well-established in the trial sites. Key components of this approach include:

• Systematic arrangements for assessing the health and social needs of people accepted into specialist mental health services

• The formation of a care plan which identifies the health and social care required from a variety of providers

• The appointment of a key worker to keep in close touch with the service user and to monitor and co-ordinate care

• Regular review and, where necessary, agreed changes to the care plan.

• Individuals will continue to receive treatment as usual, directed by the principles and CPA process outlined above.

Individuals within the control teams will continue to receive treatment as usual, as directed by the principles and CPA process outlined above.

### Intervention

The intervention comprises a 12-month, team-level pro-recovery intervention in addition to standard care. It includes recovery interventions to be carried out at both the team (cluster) and individual practitioner level. The intervention is described in detail in the REFOCUS manual (available from http://researchintorecovery.com/refocus). In summary, it involves two components:

#### A. Recovery-promoting relationships

• Training and reflection opportunities will be offered to teams to allow them to understand what personal recovery means in their context, to consider their own values and how these can support recovery, and to develop and practice the use of coaching skills.

• People who use services can be active agents in shaping the content of clinical interactions. Service users will be supported to develop expectations that their values, strengths and goal-striving will be prioritised.

• Partnership relationships recognise the professional expertise of staff and the expertise from lived experience of service users. Teams will undertake a project to develop and practise partnership working, e.g. through staff and service users doing or learning something jointly.

#### B. Pro-recovery working practices

• Understanding the service user's values and treatment preferences underpin an individualised approach to care planning. Workers will be trained in understanding values.

• Amplifying a service users' strengths and ability to acccess community supports is an important approach to supporting recovery. Workers will be trained in assessing strengths.

• Identifying personally valued goals, developing intermediate steps, and striving towards these goals contributes to recovery. Workers will be trained to use existing care planning skills to support goal-striving.

The practice change is supported by an implementation strategy, described in detail in the REFOCUS manual. In summary, the process involves six implementation components: i) Information sharing; ii) Personal recovery training; iii) Coaching and working practice training; iv) Team manager reflection groups; v) Team reflection sessions; and vi) Supervision reflection.

### Measures

#### Staff-Rated Measures

##### Generic

• The **Sociodemographics Form - Worker (SF-W) **is a staff-rated form developed specifically for the trial, which records the person's age, gender, ethnicity, languages spoken, qualifications, core profession, current role, grade, team, time since qualification, personal experience of mental illness, and experience of caring for a family member or friend with a mental illness.

• The **Recovery Knowledge Inventory (RKI) **is a 20-item staff-rated measure of staff knowledge and attitudes about recovery [34].

• The **Mental Illness: Clinicians' Attitudes (MICA) **Scale is a 16-item of attitudes towards mental illness (staff-rated) [35].

• The **Recovery Fidelity Scale - Worker (RFS-W) **is a staff-rated measure developed specifically for the trial, which assesses fidelity to the intervention elements.

• The **Implementation Scale (RIS) **is a staff-rated measure developed specifically for the trial, which assesses the experience of the six implementation strategies.

##### Service user-specific

• The **Health of the Nation Outcome Scale (HoNOS) **is a 12-item staff-rated measure of social disability [36].

• **Camberwell Assessment of Needs Short Appraisal Schedule-(CANSAS - S) **is a 22-item staff-rated assessment of health and social needs [37].

• The **Global Assessment of Functioning (GAF) **is a 3-item staff rated measure of impairment in functioning due to physical (or environmental) limitations.

#### Service User-Rated Measures

##### Outcome measures

• (Primary outcome) The **Process of Recovery Questionnaire (QPR) **is a 22-item service user-rated assessment of personal recovery [26]. Each item is rated on a five-point scale from 0 (Disagree Strongly) to 4 (Agree strongly). Two subscale scores are produced: Intrapersonal sub-scale based on 17 items (range 0 to 4, high score good) and the Interpersonal sub-scale based on 5 items (range 0 to 4, high score good). The QPR was developed in the UK and has been used with a population of people who have experienced psychosis. It has an internal consistency of r = 0.94 for the Intrapersonal sub-scale and r = 0.77 for the Interpersonal sub-scale, indicating good internal consistency. It obtained good test-re-test reliability for both sub-scales (Intrapersonal: r = 0.874, p = 0.001) and (Interpersonal: r = 0.769, p = 0.001). It also has good construct validity and correlates with the Making Decisions Empowerment Scale, Schizophrenia Quality of Life Scale and General Health Questionnaire.

• (Secondary outcome) The **Warwick-Edinburgh Mental Well-Being Scale (WEMWBS) **is a 14-item service user-rated of well-being [38].

• (Secondary outcome) The **Mental Health Confidence Scale (MHCS) **is a 16-item service user-rated measure of empowerment [39].

• (Secondary outcome) The **Herth Hope Index (HHI) **is a 12-item service user-rated measure of client levels of hope [40].

• (Secondary outcome) The **Manchester Short Assessment of Quality of Life **(**MANSA) **is a 16-item service-user rated measure of quality of life [41].

• (Secondary outcome) The **Goal setting - Personal Primary Outcome (GS-PPO) **is a service user-rated measure developed specifically for this trial, which identifies a personally-valued outcome as an alternative to the pre-defined primary outcome of the trial.

• (Secondary outcome) **Client Satisfaction Questionnaire (CSQ) **is an 8-item service user-rated measure of client satisfaction with mental health services [28].

• **Camberwell Assessment of Needs Short Appraisal Schedule-(CANSAS - SU) **is a service user-rated 22-items measure of health and social needs [37]. Both staff and service user perspectives are assessed becase they differ [42,43]

• **ICECAP-A **is service user-rated 5-item measure of overall quality of life which intended for use in economic evaluation [44].

##### Process measures

1. The **Importance of services in recovery (INSPIRE) **is a service user-rated measure of recovery orientation of services which was developed specifically for this trial.

2. The **Recovery Fidelity Scale - Service User (RFS-SU) **is a service user-rated measure developed specifically for this trial, which assesses experience of the intervention elements. Each item is rated on a five-point scale ranging from 0 (Strongly Disagree) to 4 (Strongly Agree). The Total score is calculated by summing each item and multiplying by 25. The total score ranges from 0 (low fidelity) to 100 (high fidelity).

##### Other measures

3. The **Sociodemographics Form - Service User (SF-SU) **is a service user-rated form developed specifically for the trial, which allows recording of the service user's date of birth, gender, ethnicity, languages spoken, country of birth, education, employment, marital status, and housing. It also records (in tear-off form for separate filing) a range of contact details (e.g. mobile, email, contact information for a relative) to facilitate contact with service users who are no longer on the caseload of the team at follow-up.

10. The **National Adult Reading Test (NART) **is a measure of pre-morbid level of intellectual functioning [45].

#### Researcher-Rated Measures

1. The **Brief Psychiatric Rating Scale (BPRS) **is an 18-item observer-rated measure of symptomatology which is completed with the service user [46].

2. The **Client Service Receipt Inventory (CSRI) **is a tool for collecting cost-related information about people with mental health problems for use in mental health service evaluations [47].

#### Team-Manager/leader measures

1. The **Team Characteristics Form (TC-F) **is a team manager/leader-rated form developed specifically for the trial, which records the team's key characteristics, such as caseload size, composition, type of team and support offered, and whether it has undergone any significant changes within the last 12 months.

### Trial procedures

Eligible teams will be recruited into the trial over a 12 month period, starting April 2011. Baseline data collection will start in teams four to five months prior to the start of the intervention. All staff who meet inclusion criteria in the participating teams will be asked to complete the generic staff measures: SF-W, MICA, RFS-W and RKI. Staff will identify whether each randomly identified service user meets the eligibility criteria. Eligible service users will then be approached by their Care Co-ordinator or another appropriate staff member from their team and asked whether they are willing to be contacted by researchers. If they agree to be contacted, then Clinical Studies Officers or research workers will then approach the potential participants, in liaison with staff. Potential participants will be given a detailed explanation of the study and a written Participant Information Sheet. If they are willing to participate, they will be asked to sign a consent form and complete the baseline interview, comprising: QPR, WEMBWS, MANSA, GS-PPO, CSQ, RFS-SU, INSPIRE-TEAM, NART, MHCS, HHI, CANSAS-SU, ICECAP-A, SF-SU, CSRI, and BPRS. If necessary, the baseline assessment will be spread over more than one meeting. Participants will be paid £10 for taking part and entered into a raffle competition to win a £100 gift voucher.

Following baseline assessment of the service user, their care co-ordinator or other appropriate team member will be asked to complete the three service user-specific measures: HoNOS, CANSAS-S and GAF.

Four to five months (varying across sites) after baseline data collection began, teams will be randomly allocated with 50% likelihood into either the intervention or control groups. The intention is that all baseline data will be collected before allocation, but where this is not possible any remaining baseline data will be collected post-allocation. On completion of the baseline assessments, teams will be given a £100 book voucher.

The 12-month intervention will be provided for intervention group teams only. Attendance at all training and reflection sessions will be recorded.

At the intervention mid-point (6 months) team leaders in the intervention teams will be asked to complete the RFS-W.

At the end of the intervention, all service users who completed baseline assessments will be re-contacted in liaison with their care co-ordinator. Where the service user is no longer in contact with the team, efforts will still be made to contact them for a follow-up assessment. The follow-up assessment will be conducted by the CSO or research worker, and will comprise the following measures: QPR, WEMBWS, MANSA, G-S-PPO, CSQ, RFS-SU, INSPIRE-TEAM, MHCS, HHI, CANSAS-SU, ICECAP-A, SF-SU, CSRI, and BPRS. The interviewer will guess allocation status at the end of the interview. If necessary, the follow-up assessment will be spread over more than one meeting. Participants will be paid £10 for taking part and entered into a raffle competition to win a £100 gift voucher.

After the follow-up assessment of the service user, their care co-ordinator or other appropriate team member will be asked to complete the three service user-specific measures: HoNOS, CANSAS-S and GAF. They will also identify the current primary clinical diagnosis. If the baseline staff respondent is no longer working with the service user, then the most appropriate member of staff will be asked to complete the measures instead.

All staff in intervention group teams (whether paired with service users or not) will be asked to rate RKI, MICA, RFS-W and RIS. All staff in control group teams will be asked to rate RKI, MICA and RFS-W. Any new staff in either group will also complete SF-W. The trial is planned to start in April 2011, with follow-up completed by December 2013.

A summary of the assessment measures is shown in Table 1.

**Table 1 T1:** Assessment measures in the REFOCUS Trial

Measure	Completion time (mins)	Time		
*Team managers*				

TC-F	2	B		FU

*All staff*				
SF-W	3	B		FU*
RKI	5	B		FU
MICA	5	B		FU
RFS-W	5	B	MP	FU
RIS (intervention staff only)	3			FU

*Paired staff - completed for each service user*				
HoNOS	10	B		FU
CANSAS-S	10	B		FU
GAF	3	B		FU

*Service user*				
SF_SU	2	B		FU
NART	10	B		
QPR	10	B		FU
WEMWBS	5	B		FU
MHCS	5	B		FU
HHI	5	B		FU
MANSA	10	B		FU
GS-PPO	10	B		FU
CSQ	5	B		FU
CANSAS-SU	10	B		FU
INSPIRE	10	B		FU
RFS_SU	3	B		FU
ICECAP-A	5	B		FU

*Researcher rated*				
BPRS	10	B		FU
CSRI	10	B		FU

Key:

B = Baseline

MP = Mid point 9 months after baseline, completed by team manager in intervention teams

FU = Follow up at 12 months post-baseline

* for new staff only

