### Sample size

#### Main study

The primary outcome is the Process of Recovery Questionnaire (QPR) [26]. This measure was chosen as the only service user-rated measure of personal recovery which has been developed in England and with adequate psychometric properties (described in Section 13.2). Since personal recovery is something experienced rather than assessed by an expert, a self-report measure was appropriate for clinical end-point. The timing between baseline and follow-up (*i.e*. the length of the intervention) was chosen as 12 months to allow sufficient time for team-level changes in practice to occur, be sustained, and have an impact.

The QPR has two sub-scales: intrapersonal (mean = 45.7, sd = 16.1, range 13-68) and interpersonal (mean = 14.0, sd = 3.7, 0-20). The sample size calculation is based on being able to detect a medium standardised effect size of 0.4 in both sub-scales, which equates to a difference of 6.4 points on the QPR intrapersonal subscale and 1.5 points on the interpersonal subscale.

The estimated sample size for a two-group comparison of means (alpha = 0.05, power = 0.8) is 99 per group. However, as this is a team-level intervention, the unit of randomisation is the team. An initial 29 teams (20 from SLaM, 9 from^2^gether) will be recruited, and we anticipate 17% attrition (due to team mergers or restructuring), giving a total of 24 teams (16 from SLaM, 8 from^2^gether). The same number of participants will be included from each team. Adjustment for clustering within teams assumes an intracluster correlation of 0.05, with equal numbers of clusters in each randomisation group. For 24 teams, 164 participants are needed per group, i.e. 14 participants per team. To allow for one participant (7%) drop-out per team, 15 participants per team will be recruited from the 29 teams. This drop-out rate is consistent with attrition in previous randomised controlled trials we have conducted [27].

The total initial sample is therefore 435 service users, comprising 225 in intervention and 210 in control. Based on the above attrition and clustering estimates, we anticipate this will produce an analysable sample of 336 participants, giving power to detect a medium effect size of 0.4 (alpha 0.05, power = 0.8) on both QPR sub-scales.

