#### 1. Longitudinal routine data

Longitudinal routine data will be collected from the clinical information system at six-monthly intervals starting one year before baseline and continuing until follow-up (i.e. at baseline - 12 months, baseline - 6 months, baseline, baseline + 6 months, baseline + 12 months, baseline + 18 months). At each recording point, anonymised data will be collected from the care plans for the participating service users. Each care plan entry will be rated for Topic and Responsibility, using categories developed in a previous study [48].

Topic categories comprise: Psychotropic medication; Symptoms/Relapse prevention; Care Programme Approach; Outpatient clinic; Physical health; Social needs; Emotional Support; Functional/Activities of Daily Living; Accommodation needs; Healthy Lifestyle; Financial; Employment; Education; and Carer work/Support.

Responsibility categories identify who is responsible for actions in the care plan, and comprise: Staff; Service user; Staff and service user; Carer; Staff and Carer; Service user and Carer; and Staff, service user and carer. Data will be collected for each consenting service user participant.

Anonymised data will be collected from the three clinical information system fields: Values and treatment preference; Strengths; and Personally valued goals.

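### The primary QPR follow-up has two incompatible times: 12 months after baseline, and the end of a 12-month intervention that starts 4-5 months after baseline collection opens

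*Protocol article*

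**What the plan says.** Two places put follow-up 12 months after baseline.

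- Trial procedures, Table 1 key: "FU = Follow up at 12 months post-baseline". The QPR row is marked for baseline and follow-up.
- Sample size, Main study: "The timing between baseline and follow-up (*i.e*. the length of the intervention) was chosen as 12 months". The reason given is time for team practice to change, hold and take effect.

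Other places put it at the end of the intervention.

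- Trial procedures: "Baseline data collection will start in teams four to five months prior to the start of the intervention". Allocation has the same lag: "Four to five months (varying across sites) after baseline data collection began, teams will be randomly allocated". The intervention then runs for 12 months.
- Trial procedures, on follow-up: "At the end of the intervention, all service users who completed baseline assessments will be re-contacted in liaison with their care co-ordinator".
- Analysis plan, Objective 1, also refers to outcomes when the intervention ends.

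The mid-point has two times as well. The Table 1 key says "MP = Mid point 9 months after baseline, completed by team manager in intervention teams", while the procedures text puts it 6 months into the intervention.

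The process evaluation collects routine care-plan data up to follow-up, on a six-monthly grid ending with "baseline + 6 months, baseline + 12 months, baseline + 18 months".

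**The concern.** The sample size section treats baseline-to-follow-up and intervention length as the same 12 months. They coincide only for someone assessed at the moment the intervention starts, and the procedures open baseline collection 4-5 months earlier. For most participants the two definitions therefore give different dates.

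Table 1 is the assessment schedule, so staff could reasonably book visits from it. The primary outcome would then be measured in intervention teams before the intervention had finished. Exposure at measurement would depend on how early in the window a person was assessed and, because the lead-in varies across sites, on the site. If some sites used the table and others the text, the primary endpoint would be measured at different times within one trial.

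**Working it through.** **Inputs.** Lead-in from opening of baseline collection to intervention start, L = 4-5 months, and intervention length, 12 months (both Trial procedures). Follow-up at 12 months after baseline (Table 1 key). Let t be the month of the window in which a person has baseline, from 0 to L.

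**Reproducing the plan's sample size.** For a 0.4 SD effect, two-sided alpha 0.05 and power 0.8, two independent groups need 99 each. With 14 per team and intracluster correlation 0.05, the design effect is 1 + 13 × 0.05 = 1.65, and 99 × 1.65 = 163.35, i.e. 164 per group, as stated. Also 24 × 14 = 336 and 29 × 15 = 435, as stated. The sample size arithmetic is not in dispute.

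**Follow-up at the end of the intervention.** Interval from an individual's baseline = 12 + L − t.
- t = 0: 16 months (L = 4) or 17 months (L = 5).
- t = L: 12 months.

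The range is 12-17 months, against the 12 in Table 1.

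**Follow-up at baseline + 12 months.** Intervention elapsed = 12 − (L − t).

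| Month of baseline, t | L = 4 | L = 5 |
|---|---|---|
| 0 | 8 | 7 |
| 1 | 9 | 8 |
| 2 | 10 | 9 |
| 3 | 11 | 10 |
| 4 | 12 | 11 |
| 5 | n/a | 12 |

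With baselines spread evenly, mean exposure is 12 − L/2, i.e. 10 months (L = 4) or 9.5 months (L = 5).

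**Mid-point.** Intervention month 6 falls L + 6 = 10-11 months after baseline collection opens, not 9. Nine months is intervention month 9 − L = 4-5. The key's own entries are 3 months apart (12 − 9), whereas the middle and end of a 12-month intervention are 6 months apart.

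**Illustrative power.** Assumption, not in the documents: the 0.4 SD effect accrues linearly over 12 months. With 12 teams of 14 per arm, the SE of the difference is √(2 × (1.65/14)/12) = 0.140. Power is from a noncentral t on 22 degrees of freedom.

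| Months of exposure | Effect (SD) | Power |
|---|---|---|
| 12 | 0.40 | 0.78 |
| 10 | 0.33 | 0.62 |
| 9.5 | 0.32 | 0.58 |
| 8 | 0.27 | 0.44 |
| 7 | 0.23 | 0.36 |

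The last two rows would need every participant to have baseline on the first day of the window. They are a lower bound under this assumption, not an expectation.

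**Calendar.** Assume the last team opens baseline in March-April 2012, at the end of the 12-month team recruitment that starts in April 2011. Baseline + 12 months is then March-April 2013, and end of intervention is July-September 2013. Both precede the December 2013 limit, so the calendar does not show which was meant.

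**The case against.** A reader might infer that the trial is designed to measure its primary outcome after only 7-8 months of intervention. The documents do not support that. The procedures text and Objective 1 of the analysis plan both point to the end of the intervention. The sample size sentence glosses its 12 months as the length of the intervention, which suggests that full exposure was intended. Loose wording in the table key is a fair explanation. This part of the objection stands: the defect is a contradiction, not a certain loss of exposure.

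A reader might also take the baseline + 18 months entry as a third QPR time. It is not. It belongs to a six-monthly grid for care-plan data, and 18 months is the first grid point after a follow-up at 16-17 months. It is compatible with the end-of-intervention reading and mildly supports it.

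The power figures are open to challenge too. Nothing in the protocol relates months of exposure to QPR change, and other accrual shapes would give other numbers. The mid-point mismatch affects only a fidelity scale completed in intervention teams.

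The objection does not remove the conflict. The key cannot be rescued by reading baseline as intervention start, because the mid-point would then be 6 months, not 9. Nor is this detail left to a fuller document, since the article itself states both times.

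**Conclusion.** The concern holds as an internal contradiction over the time of the primary endpoint. The Table 1 key and the sample size section say 12 months after baseline. The procedures text and analysis plan say end of intervention, which is 12-17 months after an individual's baseline. The timeline arithmetic needs only the protocol's own figures and assumes baseline is completed before allocation, as intended. Baselines collected after allocation, which the protocol permits, would shift the Table 1 follow-up past the end of the intervention.

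If Table 1 were followed, exposure at the primary assessment would run from 7-8 to 12 months. A fall in power from 0.78 to about 0.58-0.62 is what linear accrual with evenly spread baselines would give. It is an illustration and should not be quoted as an expected loss. The mid-point error is real but secondary. Because the primary outcome is affected and the remedy is cheap, the passages should be reconciled before follow-up visits are scheduled.

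**What to change.** Use one time origin throughout. Set the primary QPR follow-up at the end of the 12-month intervention, counted from the team's allocation or intervention start, with the same date rule for control teams and a stated visit window.

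- Table 1 key: restate follow-up as 12 months, and the mid-point as 6 months, after intervention start.
- Sample size, Main study: re-anchor the 12 months to intervention start. Deleting only the parenthesis would leave a 12-month baseline-to-follow-up interval, and so the contradiction.
- Longitudinal routine data: reconcile the statement that collection continues until follow-up with the chosen origin. The grid itself need not move.

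The cost is protocol wording and the visit-scheduling tool, with no extra visits or participants. On the calendar assumption above, follow-up still ends before December 2013. The downside is a baseline-to-follow-up interval of about 12-17 months that differs between participants. With baseline taken before allocation and one date rule for both arms, this variation should be alike in the two arms.
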